## Abstract

**Background:**

Total hip (THR) and total knee replacements (TKR) are two highly successful orthopaedic procedures that reduce pain for people with osteoarthritis. Previous evidence suggests that physical activity, at best, remains the same pre- to post-operatively, and in some instances declines. The PEP-TALK trial evaluates the effects of a group-based, behaviour change intervention on physical activity following a THR or TKR.

**Methods:**

PEP-TALK is an open, phase III, pragmatic, multi-centre, parallel, two-arm, two-way superiority randomised controlled trial investigating the effectiveness of usual care plus a behaviour change therapy compared with usual care alone following primary THR or TKR. The primary outcome is the UCLA Activity Score at 12 months post-randomisation which will be analysed using a linear mixed effects model. Secondary outcomes measured at 6 months and 12 months after randomisation include the UCLA Activity Score, Lower Extremity Functional Scale, Oxford Hip/Knee Score, Numerical Rating Scale for Pain, Generalised Self-Efficacy Scale, Tampa Scale for Kinesiophobia, Hospital Anxiety and Depression Scale, EuroQoL EQ-5D-5L index and EQ-VAS and complications or adverse events. Full details of the planned analysis approaches for the primary and secondary outcomes, as well as the planned sensitivity analyses to be undertaken due to the COVID-19 pandemic, are described here. The PEP-TALK study protocol has been published previously.

**Discussion:**

This paper provides details of the planned statistical analyses for the PEP-TALK trial. This is aimed to reduce the risk of outcome reporting bias and enhance transparency in reporting.

**Trial registration:**

International Standard Randomised Controlled Trials database, ISRCTN Number: 29770908. Registered on October 2018.

## Background

This analysis strategy adheres to the Statistical Analysis Plan Guidelines [1].

Total hip (THR) and total knee replacements (TKR) are two highly successful orthopaedic procedures which reduce pain for people with osteoarthritis [2, 3]. Over 230,000 THR and TKRs were performed in the UK in 2019 [2]. Approximately 90% of patients are satisfied following THR and TKR [3] with significant improvements in pain and physical function after 3 to 12 months [3, 4]. However, medical co-morbidities are common in this population. These include hypertension (56%) [5], cardiovascular disease (20%) [6], diabetes (16%) [6] and multi-joint pain (57%) [5]. Twenty-seven per cent of people who undergo joint replacement have three to four comorbidities [6]. Medical comorbidities such as these have a significant negative impact on both health-related quality of life and societal burden [7, 8].

Historically, it has been assumed that people are more active following THR or TKR through the amelioration of their joint pain [9]. However, previous evidence has indicated that physical activity, at best, remains the same from pre- to post-operatively, and in some instances declines [9]. There does not appear to be a difference in physical activity trajectories between those following THR or TKR [9, 10]. The reasons for reduced participation may differ between the groups [10] with TKR more often associated with increased pain in the initial 12 post-operative months compared to THR [3, 4], whereas those with THR may have greater fear avoidance through the risks of joint implant dislocation [3, 4].

Subsequent analyses from large USA and UK datasets have supported this finding, re-enforcing the notion that physical activity is lower after THR and TKR compared to age- and gender-matched cohorts who had not undergone joint replacement [10]. Given that physical activity can significantly reduce symptoms associated with common comorbidities [11], this population’s physical inactivity has a detrimental effect on their health. Participating in regular physical activity can decrease the risk of cardiovascular disease by 52% [12], diabetes by 65% [13] and some cancers by 40% [14] and reduces all-cause mortality by 33% and cardiovascular mortality by 35% [15]. Accordingly, supporting people to be more physically active can improve both patient’s health and decrease the economic burden these diseases place on the NHS. To date, no interventions aimed to increase physical activity following joint replacement surgery have been robustly tested. To address this, the PEP-TALK trial was undertaken.

## Methods

### Trial design

The trial is an open, phase III, pragmatic, parallel, two-arm, two-way superiority randomised controlled trial (RCT) on individuals investigating the effectiveness of usual care plus a group exercise and behaviour-change intervention versus usual care alone to increase physical activity following primary THR or TKR. Neither participants nor physiotherapists can be blinded to the treatment allocation. Primary comparison is assessed at 12 months post-randomisation with data being collected at baseline (pre-operatively), 6 months and 12 months post-randomisation.

Participants will be screened for inclusion in the trial pre-operatively, consented pre-operatively and eligibility confirmed post-operatively. They will then be randomised prior to hospital discharge and notified of their group allocation to facilitate the organisation of their rehabilitation. Initially, participants were randomised to the two groups 1:1 using minimisation by trial centre, type of joint replacement (THR or TKR), and Charlson co-morbidity index (1–3 or ≥4). The minimisation algorithm will have a probabilistic element of 0.8 included to ensure unpredictability of treatment assignment.

After 75 randomisations, the random allocation ratio was changed to 2:1 (Experimental Intervention: Usual Care). This change was made to ensure more participants were randomised to the experimental intervention group. The intervention is group-based and is designed to have three or more participants per group session. Based on evidence from early recruiting sites, there was difficulty to consistently fill sessions under a 1:1 allocation ratio. Therefore this change was deemed important to facilitate larger groups. This change was implemented by the Trial Management Group and approved by the Data Safety Monitoring Committee, Sponsor and Research Ethics Committee.

Those randomised to usual care (the comparator) will receive six, 30-min group-based exercise sessions. Those randomised to the experimental intervention will receive six group-based behaviour change intervention sessions (30-min duration) immediately followed by the control intervention of 30 min of group-based exercise and three follow-up telephone calls up to 6 weeks after completing the group sessions. Both group’s physiotherapy will commence within the initial four weeks post-randomisation and continue weekly for 6 weeks. Further details of the trial design and procedures, including full eligibility criteria and trial interventions are found in the PEP-TALK trial protocol [16].

### Outcomes

#### Primary outcome

The primary outcome measure is the UCLA Activity Score 12 months post-randomisation. The UCLA Scale is a reliable and valid self-reported tool to assess physical activity [17, 18] that assesses global activity levels with a grading system of 1 to 10 where 1 equates to “wholly inactive, dependant on others and cannot leave residence” and 10 refers to “regularly participates in impact sports”.

#### Secondary outcomes

The secondary outcome measures, self-reported with partial answers being coded as missing and collected at baseline (except complications), 6 and 12 months post-randomisation unless otherwise stated, are as follows:
*Functional outcome:* Lower Extremity Functional Scale (LEFS) [19]. A questionnaire containing 20 questions scored using a scale 0-80 with a higher score representing a higher functional level.*Disease specific function:* Oxford Hip Score/Oxford Knee Score (OHS/OKS) [20, 21]. A 12-item disease-specific questionnaire, scores range from 0 to 48 where 48 indicates high joint function. Murray et al. [22] recommends to impute the mean value representing all other items to fill in two or fewer missing items.*Perceived level of pain*: Numerical Rating Scale (NRS) for Pain. An 11-point scale where participants mark their perceived pain between 0 representing ‘no pain’ to 10 representing the ‘worst possible pain’.*Self-efficacy:* Generalized Self-Efficacy Scale (GSES) [23]. A 10-item scale with scores ranging from 10 to 40, higher scores representing a high level of self-efficacy.*Fear avoidance:* Tampa Scale for Kinesiophobia [24]. A 17-item self-completed questionnaire with scores from 17 to 68 where the higher scores indicate an increasing degree of kinesiophobia.*Psychological distress:* Hospital Anxiety and Depression Scale (HADS) [25]. This scale consists of 14 items divided into two 7-item subscales: Anxiety and Depression. The total score is out of 42 (21 per subscale), higher scores indicate greater levels of anxiety/depression or global psychological distress.*Health-related quality of life:* Euroqol EQ-5D-5L [26]. A patient-reported health-related quality of life questionnaire consisting of two parts. First, five domains related to daily activities with a 5-level answer possibility are measured [26, 27], which will be converted into multi-attribute utility scores using established algorithm [28]. To calculate EQ-5D-5L Index scores the Crosswalk Index Value Calculator will be used to map the 5L descriptive system data onto the 3L dataset using the mapping function developed by van Hout et al. [27] as, at the time of writing this statistical analysis plan, there is still debate about the appropriate value set for the 5L. Secondly, the Euroqol VAS (EQ-VAS) is a 0 to 100 visual analogue score from the worse (0) to best health imaginable (100). Any participant who dies will have their EQ-5D-5L Index imputed as a score of zero for all time points after death, their EQ-VAS scores will be missing data for those time points.Complications and adverse events will be collected throughout the trial.

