##### Missing data

Missing data analysis will be performed on the primary outcome only. The primary analysis multi-level model using repeated measures is relatively robust to missing data under the missing at random (MAR) assumption [30].

Analysis will be performed on an intention-to-treat basis. The number and percentage of participants in the missing category will be presented, as well as reasons for missingness if known. Missing data will be reported and summarised by the treatment group. The distribution of missing data will be explored to assess the assumption of data being missing at random under which the principal analyses will be conducted. Varying scores of the UCLA Activity Score (e.g. 30th, 40th, 50th, 60th, 70th quantiles) will be imputed where data is missing and these ‘complete’ datasets will be reanalysed, using the same model used in the primary analysis and the results presented in graphical form. This analysis will be undertaken if there is more than 5% missing data for the primary outcome at 12 months.

If there is evidence that there is a departure from the MAR assumption, a search for factors not included in the primary analysis model that explains missingness will be performed and if variables are found, multiple-imputation using chained equations [31] will be utilised, using the primary analysis model but including these variables to assess the sensitivity of the findings to missing data. If no variables are identified, multiple-imputation will not be performed.

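### The SAP leaves two ways to score an Oxford questionnaire with one or two blanks, and its complete-or-missing rule may discard usable LEFS, Tampa, HADS and GSES scores

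*SAP article*

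**What the plan says.** The Secondary outcomes section opens its list of measures with one sentence that covers them all. It calls them "self-reported with partial answers being coded as missing" and then gives the collection times, ending "6 and 12 months post-randomisation unless otherwise stated, are as follows".

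The Oxford Hip/Knee Score entry ("A 12-item disease-specific questionnaire, scores range from 0 to 48") adds that a cited source "recommends to impute the mean value representing all other items to fill in two or fewer missing items". It does not say whether the trial adopts this.

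The entries for LEFS ("A questionnaire containing 20 questions scored using a scale 0-80"), GSES ("A 10-item scale with scores ranging from 10 to 40"), the Tampa Scale (17 items) and HADS (14 items in two subscales of seven) give no rule for blank items, so the general rule governs them.

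Two later sections bear on the consequence. Analysis of the secondary outcomes uses mixed models over 6 and 12 months, with the baseline score of the same measure as a covariate. The Missing data section says: "Missing data analysis will be performed on the primary outcome only".

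**The concern.** For an Oxford score with one or two blanks, the introductory sentence gives a missing value and the cited recommendation gives a number. Two analysts following the SAP could build different Oxford datasets. The article says that it aims to reduce the risk of outcome reporting bias, so a scoring choice should not be left open.

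For LEFS, Tampa, HADS and GSES the rule is explicit, and it discards observed answers. One blank among 20 LEFS items voids the other 19. At follow-up this costs one score at one visit. At baseline it removes the covariate, and unless missing baselines are handled separately, the participant drops out of that outcome's model at both visits. The same rule reaches the mediation analysis (Additional analysis), where self-efficacy, fear avoidance and psychological distress are among the mediators. No planned sensitivity analysis would show the effect, because missing-data work is confined to the primary outcome.

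**Working it through.** **Two readings of an Oxford form with 1 or 2 blanks**
- General rule: the form is partial, so the score is missing.
- Cited recommendation: the blanks take the mean of the answered items, so the score is kept.

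The qualifier at the end of the introductory sentence follows the visit times and most naturally belongs to them. It could also cover the missing-answer rule. The text does not decide.

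**How many forms could be affected**

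The SAP gives no expected rate of incomplete forms, so there is no figure of its own to reproduce. The item counts *k* come from the Secondary outcomes section. The per-item missing rate *p* is an assumption.

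If blanks are independent, P(at least one blank) = 1 − (1 − *p*)^*k*. For LEFS at *p* = 1%: 1 − 0.99^20 = 18.2%.

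| Scale (items) | p = 0.1% | 0.5% | 1% | 2% |
|---|---|---|---|---|
| LEFS (20) | 2.0% | 9.5% | 18.2% | 33.2% |
| Tampa (17) | 1.7% | 8.2% | 15.7% | 29.1% |
| HADS total (14) | 1.4% | 6.8% | 13.1% | 24.6% |
| Oxford (12) | 1.2% | 5.8% | 11.4% | 21.5% |
| GSES (10) | 1.0% | 4.9% | 9.6% | 18.3% |

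For scale, 230 randomised (Trial status) with the 20% loss assumed in the Sample size section gives 230 × 0.8 = 184 returned forms. LEFS would then lose about 4, 18, 33 or 61 of them per visit across the four rates.

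**If blanks cluster within people**

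A beta-binomial with the same mean rate and an assumed intra-person correlation of 0.3 gives, for LEFS, 2.8%, 5.6% and 10.9% of forms with any blank at *p* = 0.5%, 1% and 2%.

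**What the Oxford choice decides**

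Oxford forms with exactly 1 or 2 blanks are those on which the two readings differ. At *p* = 0.5%, 1% and 2% they make up 5.8%, 11.3% and 21.4% of forms if blanks are independent, and 1.5%, 2.9% and 5.6% if clustered (correlation 0.3).

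**What limited imputation could recover**

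Take a two-item limit on LEFS at *p* = 1%. If blanks are independent, 18.1 of the 18.2 percentage points are recovered. If they cluster, 3.1 of the 5.6 points are recovered, and the rest have more than two blanks.

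**Baseline**

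A 12-month LEFS analysis with a baseline covariate needs 40 answered items. At *p* = 1% and independence, 1 − 0.99^40 = 33% of participants who return both forms would lack one complete score or the other.

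**The case against.** *The qualifier makes the Oxford entry an exception.* A general rule followed by an instrument-specific one is a common layout, and the EQ-5D-5L entry does something similar for deaths. This has force, and it is why a reader who infers a flat contradiction goes further than the text supports. But the Oxford entry reports what a source recommends rather than what the trial will do, so the question stays open even on that reading.

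*Complete-or-missing is a legitimate choice.* It is prespecified, reproducible and conservative, and for LEFS, Tampa, HADS and GSES it conflicts with nothing else in the SAP. That stands: the rule is not an error. The point is that it costs data which a limited rule would keep.

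*The loss may be small.* A reader might infer that many scores would be lost. The document does not support that, because the item-missing rate is unknown and clustering cuts the loss sharply. The mixed model also keeps a participant's other follow-up score when the baseline score is present.

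*A power loss cannot be claimed.* One might carry the 0.4 standardised effect in the Sample size section over to these outcomes. That target belongs to the primary outcome. No secondary outcome has a power target, and a single-visit comparison does not represent the planned baseline-adjusted model over two visits.

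*A flat two-item rule may not suit every scale.* This also stands. Two items are 2/7 = 29% of a HADS subscale, so a limit should be in proportion to scale length.

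**Conclusion.** Minor. Two things hold whatever the missing rate. The derivation of Oxford scores with one or two blanks is unresolved, and the stated rule voids a LEFS, Tampa, HADS or GSES score for a single blank item, at baseline as well as follow-up, with no planned sensitivity analysis.

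How much is lost cannot be known from the SAP. For LEFS, the longest scale, the range is about 2% to 33% of forms per visit at 0.1% to 2% per item under independence, and about 3% to 11% at 0.5% to 2% with a within-person correlation of 0.3. Both the rates and the correlation are assumptions. The supportable wording is that the rule may discard usable scores.

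The primary outcome is a single UCLA grade and is not touched. NRS pain and EQ-VAS are single items and are not at issue.

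**What to change.** Before data lock, amend the Secondary outcomes section as follows:

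- State that OHS/OKS follow the two-item mean-imputation rule, as an exception to the general rule.
- For LEFS, Tampa, GSES and each HADS subscale, name one limited missing-item rule: the instrument's published rule where there is one, otherwise person-mean imputation up to a small fixed limit in proportion to the length of the scale or subscale. Beyond the limit the score is missing.
- Apply the same rule at baseline as at follow-up.
- Keep NRS, EQ-VAS and an incomplete EQ-5D-5L profile as missing.
- Report the number of prorated scores by arm.

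The cost is one paragraph and a few lines of scoring code, with no new data. The downside is a mild reliance on consistency between items within a scale for the prorated forms.

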
### Sample size

Two hundred fifty participants (125 per arm) are required to detect a standardised effect size of 0.4 with 80% power and 5% (2-sided) significance, allowing for 20% loss to follow-up. These calculations are based on the primary outcome at 12 months post-randomisation, assuming a baseline standard deviation of 2.5 [17] and a between-group difference of one. Our target standardised effect size is derived from the UCLA Activity Score’s minimal clinically important difference of 0.92 [17]. The sample size was increased to 260 to account for the change in allocation ratio, maintaining the same power and type I error rate.

*Note:* The terms ‘COVID-19 status’ and ‘pre-COVID-19/COVID-19’ groups used within this paper refer to the definitions outlined in the ‘Definition of analysis populations’ section. This does not refer to participants who tested positive for COVID-19; testing information has not been collected as part of this trial.

### Statistical analysis

#### General analysis principles

There is one planned final analysis, which will occur 12 months after the final participant’s randomisation, allowing for an appropriate time for the data to be collected, cleaned and prepared for final analysis. There is no multiple testing as only a single primary outcome is considered. Significance levels used will be 0.05 and 95% confidence intervals will be reported. Any analyses not pre-specified will be exploratory in nature and a significance level of 0.01 will be used to declare statistical significance and 99% confidence intervals will be presented. No formal interim analysis or predefined early stopping rules are planned for this trial.

#### Definition of analysis populations

*Intention-to-treat:* inclusion of all available randomised participants who will be analysed in the groups to which they were randomly allocated irrespective of non-compliance. If a participant has observed data on any of the follow-up time points, they will be included in the analysis.*Per protocol:* eligible participants who received the treatment they were randomised to with data on the primary outcome at 12 months. Participants who had major protocol violations/deviation (e.g. not have received the treatment they were allocated to) will be excluded from this population.*Strict compliers:* participants who fall under the Strict Compliance definition outlined in the ‘Compliance’ section.*Compliers:* participants who fall under the Compliance definition outlined in the ‘Compliance’ section.*Attenders:* participants who fall under the Attendance definition outlined in the ‘Compliance’ section.*Pre-COVID-19:* participants who completed their intervention before national UK lockdown (23rd March 2020) and had no disruption to their planned treatment.*COVID-19:* participants who did not receive any intervention before 23rd March 2020 or had their intervention delivery disrupted by the UK lockdown.

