#### Analysis of the primary outcome

The primary outcome measure, the role of usual care versus usual care plus the experimental intervention upon the UCLA Activity Score at 12 months post-randomisation, will be modelled using a mixed effects model. This model will account for person within centre random effects, and Charlson Comorbidity Index score and baseline UCLA Activity Score (as continuous outcomes), type of operation the patient is undergoing (THR or TKR), time (6 or 12 months) and treatment as fixed effects. Treatment by time point interactions will also be included in the model to allow time-specific treatment effects to be calculated. This model uses all available data at each time point. Comparison will be performed on an intention-to-treat basis and results presented as comparative summary statistics (i.e. difference in means) with 95% confidence intervals.

The appropriateness of the assumption of approximate normality of the residuals of this model will be assessed graphically. If the residuals are not normally distributed, the outcome data will be log-transformed to gain normality and geometric means with 95% confidence intervals will be reported. If data is not normally distributed after log-transformation, the non-parametric Mann-Whitney test will be used with no adjustment for baseline or stratification factors, and the difference in medians with 95% confidence intervals will be reported.

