#### Analysis of the secondary outcomes

The continuous secondary outcomes, to compare functional outcomes, disease-specific function, perceived level of pain, self-efficacy, fear avoidance, psychological distress and health-related quality of life between groups, are assessed through the corresponding PROMs measured at baseline, 6 months and 12 months post randomisation. Mixed effects models, as used in the primary analysis, will be used to assess these outcomes. These models will account for person within centre random effects, and Charlson Comorbidity Index score and the relevant baseline PROM score (as continuous outcomes), operation type, time (6 or 12 months) and treatment as fixed effects. Treatment by time point interactions will also be included in the model to allow time-specific treatment effects to be calculated.

There is expected to be a low number of complications/serious adverse events (SAEs) in this trial. Any adverse events (AEs) occurring whilst a participant is continuing in the study, until completion of the final study visit will be recorded. All AEs will be reported and tabulated by grade and treatment group—similar reporting will be done with SAEs. The number of SAEs and the number of participants reporting one or more SAEs will be reported by the treatment group. If there is a large enough number of events for a comparison to be appropriate, then the complications in each group will be pooled and the ‘Total Complications’ analysed by calculating the odds ratio and 95% confidence interval using logistic regression adjusting for minimisation factors (recruiting centre, Charlson Comorbidity Index (as a continuous value) and type of operation) and treatment.

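### The stated analysis set admits anyone with a follow-up score, but the models need a baseline score, and no rule covers a missing one, chiefly on the multi-item secondary scales

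*SAP article*

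**What the plan says.** **Who is analysed.** Under Definition of analysis populations, the intention-to-treat entry reads: "If a participant has observed data on any of the follow-up time points, they will be included in the analysis". It does not mention baseline.

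**The models.** Under Analysis of the primary outcome, the covariates include "Charlson Comorbidity Index score and baseline UCLA Activity Score (as continuous outcomes"; time has two levels, 6 and 12 months, and the section adds: "This model uses all available data at each time point". Under Analysis of the secondary outcomes, the same structure is used with "Charlson Comorbidity Index score and the relevant baseline PROM score (as continuous outcomes), operation type, time (6 or 12 months) and treatment as fixed effects".

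**How a score becomes missing.** Under Secondary outcomes, the measures are "self-reported with partial answers being coded as missing and collected at baseline (except complications), 6 and 12 months post-randomisation". For the Oxford scores only, the same section cites a source that "recommends to impute the mean value representing all other items to fill in two or fewer missing items".

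**What is done about missing data.** The Missing data section limits its work to the primary outcome. Its imputation of UCLA quantiles is triggered by more than 5% missing at 12 months, and its multiple imputation is conditional on evidence against missing at random and on finding explanatory variables. No section says what happens to a participant whose baseline score is missing.

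**The concern.** A repeated-measures mixed model copes with missing outcomes because each participant contributes whatever visits were observed. It does not cope with a missing covariate: without the baseline score, none of that participant's rows can enter the likelihood, even when both follow-up scores are present. The robustness under missing at random that the plan claims for its model concerns the repeated outcome, not the covariate.

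The definition of the analysis set and the model specification therefore disagree for anyone with follow-up but no baseline score. The plan's own scoring rule produces such people on the multi-item secondary scales, since one blank item at baseline removes the score. The Descriptive analysis section itself expects some individual items to go unanswered.

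At stake are precision on the secondary outcomes, in a trial that closed at 230 of 260, and a set labelled intention-to-treat that is in fact complete-case on baseline and differs from one outcome to the next.

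**Working it through.** **1. The plan's own figures.** The Sample size section gives a standardised effect of 0.4 (difference 1, SD 2.5), 80% power, two-sided 5% and 20% loss. The normal approximation gives 2 × (1.960 + 0.842)² / 0.4² = 98.1, so 99 per arm; 99 / 0.8 gives 124 per arm, 248 in total. The t-test version gives 100 per arm and 200 / 0.8 = 250, as stated. With 75 randomised 1:1 and the rest 2:1, 260 with 20% loss gives 80.0% power. The plan's figures reproduce and are not in dispute.

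**2. Number followed up.** 230 were randomised (Trial status). Applying the planned 20% loss, 230 × 0.8 = 184. That this loss rate applies is an assumption.

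**3. Does the conflict occur in practice?** Data were simulated for 184 participants, all with both follow-up scores, and baseline was deleted for 18. The model with baseline as covariate, fitted to the rows with a complete covariate, kept 166 participants (332 rows). The intention-to-treat definition would include all 184.

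**4. How many might be affected.** Item counts come from the Secondary outcomes section, except the five EQ-5D domains, each counted as one item. The per-item skip rate p is assumed, with skips independent. The share with at least one blank among k items is 1 − (1 − p)^k; the count is that share × 184.

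| Scale (k) | p = 0.25% | p = 0.5% | p = 1% |
|---|---|---|---|
| LEFS (20) | 4.9% (9.0) | 9.5% (17.6) | 18.2% (33.5) |
| Tampa (17) | 4.2% (7.7) | 8.2% (15.0) | 15.7% (28.9) |
| HADS total (14) | 3.4% (6.3) | 6.8% (12.5) | 13.1% (24.2) |
| HADS subscale (7) | 1.7% (3.2) | 3.4% (6.3) | 6.8% (12.5) |
| GSES (10) | 2.5% (4.5) | 4.9% (9.0) | 9.6% (17.6) |
| EQ-5D index (5) | 1.2% (2.3) | 2.5% (4.6) | 4.9% (9.0) |
| Single rating (1) | 0.25% (0.5) | 0.5% (0.9) | 1.0% (1.8) |

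For the Oxford scores with up to two items filled, the loss needs three or more blanks among 12, which is below 0.2% even at p = 2%.

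**5. Cost in precision for LEFS.** Dropping a share d multiplies the standard error by (1 − d)^−0.5: a rise of 2.5%, 5.1% and 10.6% at d = 4.9%, 9.5% and 18.2%. If the participants are kept with a filled baseline and an indicator, the information is (1 − d) + d(1 − r²). With an assumed baseline-outcome correlation r = 0.5, the rise is 0.6%, 1.2% and 2.4%. That formula weights the two subsets optimally. With one common residual variance the factor is √(1 + d·r²/(1 − r²)), for example √(1 + 0.182 × 0.25/0.75) = 1.030, a rise of 3.0%.

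A simulation (184 analysed, 3000 runs) at d = 0.18 gave standard deviations of the estimate of 0.143 when dropping, 0.134 with fill plus indicator, and 0.129 with full baseline. These are rises of 10.9% and 3.9%. At d = 0.10 the first two were 0.139 and 0.133, rises of 7.8% and 3.1%. Each standard deviation carries a Monte Carlo error of about 1/√6000 = 1.3%, so the simulation agrees with the formulas only roughly. Both methods were unbiased (mean estimate 0.40).

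**6. Primary outcome.** With 230 randomised and 20% loss, power on the plan's assumptions is 75.3%. A further 1%, 2% or 5% without a baseline UCLA score would make it 74.9%, 74.4% or 73.1%.

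**The case against.** The document nowhere says that these participants are dropped. That is the default behaviour of the model, and the text is merely silent. An article condenses a longer plan, and covariate handling might be set there. The silence is conceded, and silence alone would not be a finding. What stands is that the article does state an inclusion rule, a model and a missing-data section, and the three do not fit together for the secondary outcomes.

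A reader might go further and infer that one blank item also removes people from the primary analysis. The documents do not support this: the rule on partial answers is stated for the secondary measures, and UCLA is described as a single grade from 1 to 10, lost only if the whole answer is absent. Nor is UCLA wholly without cover. The area-under-the-curve model moves baseline into the time effect and could keep such participants, and the Missing data section offers quantile and conditional multiple imputation. These are supporting or conditional analyses and concern UCLA only. The promised reasons for exclusion from the primary analysis would also make a gap visible there, but not for the secondary outcomes.

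A reader might also count the Oxford scores as affected. If the cited allowance is applied, they hardly are.

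The magnitudes are open to challenge. The skip rates are assumed, independence overstates the loss if blanks cluster in the same people, and HADS loses less if its subscales are analysed separately. All of this stands.

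**Conclusion.** The point holds for LEFS, Tampa, HADS, GSES and the EQ-5D index: fitted as specified, their models would not analyse the set that the plan defines. It holds only to a minor extent for UCLA, pain NRS and EQ-VAS (single ratings), and hardly at all for the Oxford scores if the two-item allowance is used.

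Assuming independent skips of 0.25% to 1% per item and 184 followed up, about 5% to 18% (9 to 34 people) would leave the LEFS model and about 2.5% to 10% the GSES model. The LEFS standard error would rise by 2.5% to 10.6%. The true number is unknown and would be smaller with clustered skips.

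A reader might infer that the treatment effects would be biased. The plan gives no ground for that: baseline is collected before surgery and randomisation follows it, so leaving people out on a missing baseline score does not in itself disturb the randomised comparison. The loss is in precision and in the match between label and analysed set. It falls mainly on secondary outcomes, but the remedy is nearly free and worth making.

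**What to change.** Under Analysis of the primary outcome and Analysis of the secondary outcomes, add that a participant with any follow-up score but a missing baseline score stays in the model. Replace the missing baseline with the mean of that baseline score pooled over both arms, and add a missing-baseline indicator as a covariate. An equivalent method that uses neither allocation nor outcome would serve as well. Report, for each outcome, the number handled this way. The analysed set then matches the intention-to-treat definition.

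The cost is a sentence in the plan and one or two lines of code per model, with no new data. The small downside is one extra covariate per model.
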